### Sample size calculation

The sample calculation was performed to detect an intergroup difference of 5 points at KHQ domains [23] (incontinence impact, daily activities limitations, physical and social limitation, personal relationship, emotions and sleep/energy). An estimated standard deviation of 10 points was adopted, considering three groups, significance level of 5%, power of 85%, and effect size of 0.25. Considering a possible sample loss of 10%, 4 participants will be added per group. Thus, the sample will be composed of 132 women (44 per group).

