### Statistical analysis plan

The statistical analysis will be performed by a researcher without involvement in the evaluations and treatment intervention. The software SPSS 16.0 and R 3.5.1 will be used for the analysis of data. The level of significance will be set at 5%. The normality of the residues will be verified by the Shapiro-Wilk test.

The comparison of SUI, voiding habits, and quality of life between groups CG, IG 1, and IG 2 and between stages (pre-treatment, re-assessment after finished the intervention protocol and follow-up), as well as the interactions between groups, will be performed by means of analysis of variance (ANOVA) of mixed models considering group and time factors for repeated measures, if the residuals present normality with post hoc contrasts (group IG1 and IG2 versus group CG, and group IG1 versus group IG2).

The first statistical procedure will verify, in general and at each evaluation stage (pre-treatment, re-assessment after finished the intervention protocol and follow-up), if SUI urine loss per day related to stress (e.g., coughing, sneezing, physical exercise or household activities) and quality of life differ into the three groups. The null hypothesis is that all groups will present equal results during outcomes assessments. The alternative hypothesis is that IG 1 will differ from CG and that IG2 will differ from the CG as well.

The second statistical procedure aims to verify if there is alteration in the SUI, urine loss per day related to stress (e.g., coughing, sneezing, physical exercise or household activities), and quality of life throughout the four stages of study evaluation (pre-treatment, re-assessment after finished the intervention protocol and, follow-up of the 3rd and 6th month) within each of the groups. The null hypothesis is that the behavior is the same throughout the stages in each group. The alternative hypothesis is that there is a difference in the stages in each group.

The quantitative variables will be presented as minimum value, maximum value, mean, median, and standard deviation. Categorical variables will be presented as frequencies and percentages.

Details of the statistical analyzes are as follows:

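### The printed sample size inputs do not give 85% power at 40 evaluable women per group; that figure needs an unstated repeated-measures assumption and an f of 0.25 that does not follow from 5/10 with three groups

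*Protocol article*

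**What the plan says.** The section Sample size calculation in the protocol article gives the target first: "The sample calculation was performed to detect an intergroup difference of 5 points at KHQ domains". It continues: "An estimated standard deviation of 10 points was adopted, considering three groups, significance level of 5%, power of 85%, and effect size of 0.25". The loss allowance and total follow: "Considering a possible sample loss of 10%, 4 participants will be added per group" and "Thus, the sample will be composed of 132 women (44 per group". The number before the allowance is therefore 44 − 4 = 40 per group, 120 in all.

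The section Statistical analysis plan describes the main comparison as "analysis of variance (ANOVA) of mixed models considering group and time factors for repeated measures", with post hoc contrasts of each intervention group against the control group and of IG1 against IG2. Group differences are to be examined "in general and at each evaluation stage (pre-treatment, re-assessment after finished the intervention protocol and follow-up". The section Evaluation tools treats a 5-point change in a KHQ domain as the smallest clinically important one.

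**The concern.** A reader who enters the printed inputs into an ordinary three-group or two-group calculation does not get 40 per group, so either an input is wrong or an assumption that drives the result is not shown. The effect size also looks like half of 5/10. That is how a standardised difference becomes f with two groups, but the trial has three.

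The stated power affects how a null result is read. The study hypothesis in the Introduction is that both active treatments work well and that PFMT alone is preferable on cost-effectiveness. A non-significant IG1 versus IG2 contrast would fit that hypothesis. If the trial is believed to have 85% power for 5 points, such a result looks more informative than it is.

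**Working it through.** **Inputs.** From Sample size calculation: difference 5, SD 10, k = 3 groups, alpha 0.05, target power 0.85, effect size 0.25, n = 40 per group, N = 120. I read 0.25 as Cohen's f, because d = 5/10 = 0.5 and d/2 = 0.25. Pairwise tests are taken as two-sided. Correlations between repeated measurements are not in the document and are assumptions throughout.

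**1. Reproducing 40 per group.** For the between-group effect in a repeated-measures ANOVA with m measurements and common correlation ρ, the noncentrality is λ = N f² m / [1 + (m − 1)ρ], on 2 and N − 3 degrees of freedom. With m = 3 and ρ = 0.5:
- λ = 120 × 0.0625 × 3/2 = 11.25; power = 0.851.
- At 39 per group (N = 117) power is 0.842, so 40 is the smallest number that reaches 0.85.

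The plan's figure is reproduced exactly, but only with m and ρ supplied from outside the paragraph. Other settings come close: m = 2 with ρ = 0.3 gives 39 per group, and m = 4 with ρ = 0.5 gives 38.

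**2. The printed inputs at one time point.**
- Three-group F test, f = 0.25: λ = 120 × 0.0625 = 7.5; power = 0.676. Reaching 85% takes 60 per group.
- Pairwise t test, d = 0.5: noncentrality = 0.5 × √(40/2) = 2.236; power = 0.598. Reaching 85% takes 73 per group (72 by the normal approximation).
- Difference detectable with 85% power at 40 per group: d = 0.678, that is 6.8 points at SD 10.

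**3. The value of f for three groups.** If 5 points is the largest difference among three means and SD is 10:
- evenly spaced means: f = 0.5/√6 = 0.204;
- two groups equal and one 5 points away: f = 0.5 × √2/3 = 0.236.

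No arrangement of three means with a range of 5 gives f = 0.25. Putting these values into the test of step 1:

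| f | λ at N = 120, m = 3, ρ = 0.5 | Power |
|---|---|---|
| 0.250 (as printed) | 11.25 | 0.851 |
| 0.236 | 10.0 | 0.805 |
| 0.204 | 7.5 | 0.676 |

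**4. If pre-treatment is one of the three measurements.** Randomised groups should not differ before treatment. An effect present at two of three stages averages to two thirds: f = 0.25 × 2/3 = 0.167, λ = 120 × 0.02778 × 1.5 = 5.0, power = 0.49.

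**5. Sensitivity to ρ in the test of step 1, m = 3, full effect at all three measurements.**

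| ρ | f = 0.25 | f = 0.236 | f = 0.204 |
|---|---|---|---|
| 0.3 | 0.92 | 0.89 | 0.78 |
| 0.5 | 0.85 | 0.80 | 0.68 |
| 0.6 | 0.81 | 0.76 | 0.63 |
| 0.7 | 0.78 | 0.73 | 0.59 |

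**6. Pairwise power with baseline adjustment.** Adjustment reduces the SD to 10√(1 − ρ²), so d = 0.5/√(1 − ρ²). At 40 per group:
- ρ = 0.5: d = 0.577, power 0.72;
- ρ = 0.6: d = 0.625, power 0.79;
- ρ = 0.68: d = 0.682, power 0.85.

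**The case against.** The strongest reply is that 40 per group comes out exactly from a repeated-measures test, and that repeated-measures ANOVA is what the Statistical analysis plan section proposes. A one-way F test or an unadjusted t test at one visit is not the planned main analysis. A reader might infer from step 2 that the trial's power simply is 60% to 68%. The documents do not support that. Those are the powers of two particular single-time-point tests, and a longitudinal or baseline-adjusted analysis can do better. KHQ reproducibility in the psychometric table runs from 0.60 to 0.82 for most of the sized domains, and a pairwise baseline-adjusted comparison reaches 85% at a correlation near 0.68. Those are reproducibility coefficients, so they are probably an upper guide to correlation across ten weeks of treatment. The plan also describes ANOVA with pre-treatment as a stage, not adjustment for it.

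A reader might also take it as established that the calculation counted pre-treatment among its three measurements. That is an inference. The Statistical analysis plan section does list three stages that include pre-treatment. But the KHQ is also scheduled at three points after treatment (end of the sessions, month 3 and month 6), and a calculation on those would give 0.851 without assuming any baseline difference. The 49% figure is therefore conditional.

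Finally, a journal article may leave the test and the correlation to a fuller document, so their absence alone is not a fault. This defends the silence, but not the value of f. With three groups, 5/10 does not give 0.25 under any test, and at the correlation that reproduces 40 per group the corrected f falls short of 85%.

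**Conclusion.** Wrong as written. The stated target and inputs do not deliver the stated 85% with 40 evaluable women per group.

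- At one time point, power is about 68% (F test, f = 0.25) or 60% (pairwise 5 points, no baseline adjustment).
- The 85% is recovered by a three-measurement between-group test at an assumed correlation of 0.5. It then falls to 68% to 80% once f matches a 5-point range across three groups.
- It is about 49% at f = 0.25 if one of those measurements is pre-treatment.

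These results rest on SD 10, 5% alpha (two-sided for pairs), 40 per group and, for the repeated-measures figures, a common correlation. A lower correlation would raise power: at 0.3 the corrected f gives 78% to 89%. No single replacement figure is therefore the trial's power without naming the analysis. The point does not show that 132 women is the wrong number to recruit, only that the claim attached to it is not supported.

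**What to change.** Keep 132 women. In Sample size calculation, replace the effect size of 0.25 with the f that follows from three assumed group means. Restate power for the contrast on which conclusions will rest, naming the test, the measurements that enter it and the assumed correlation. For example:

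*With 40 evaluable women per group, power for a 5-point pairwise difference at SD 10 at one time point (two-sided 5%) is about 60% without baseline adjustment, and 85% for a difference of 6.8 points. With baseline adjustment, power for 5 points is about 72% at a baseline correlation of 0.5, 79% at 0.6 and 85% at about 0.68.*

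The second sentence belongs only if the analysis is changed to adjust for baseline. If a repeated-measures group effect is kept as the basis, the paragraph should say whether pre-treatment is among the measurements.

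The cost is one rewritten paragraph and no extra participants. The only downside is a less favourable stated power.

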### Randomization and allocation

Once included, the initial assessments will be carried out before the participants are randomized (1:1:1) into three groups (CG (control group without physiotherapist-guidance booklet related to PFMT), IG 1 (intervention group 1, that will perform PFMT with physiotherapist supervision once a week), and IG2 (intervention group 2, that will perform PFMT + NMES with physiotherapist supervision once a week)), using the electronic system “Randomization Main.” One researcher, who will not be involved into the participants’ recruitment or treatment, will perform the randomization by the electronic system and will maintain the randomization numeric sequence inside opaque envelopes (Fig. 1). After the assessment of the eligibility, one physiotherapist responsible for the application of the interventions will open one sealed opaque envelope (containing the proposed treatment and the code of “Randomization Main”) and will schedule the date to the beginning of treatment as specified by one of the three groups.

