## Methods

### Trial design

This is study is a randomized controlled trial with a blind assessor and economic evaluation. Outcome measures will be assessed at baseline (before treatment begins), on the last day of treatment (after the 10th session), and up to 6 months after the treatment is completed (follow-up). From January 2022, participants will be invited and randomized into three groups by a simple randomization using an electronic system “Randomization Main” and a ratio of 1:1:1. The data for the primary outcome will be collected until the end of 2023 and the follow-up data until the first semester of 2024. This project will follow the guidelines of the *Consolidated Standards of Reporting Trials* (CONSORT) and *Standard Protocol items: recommendations for interventional trials* (SPIRIT) [15] items.

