A semistructured questionnaire will be used to assess the economic data related to the health services use. In addition, the use of medications, history of medical consultation and/or emergency care, history of hospitalizations related to urinary problems, and surgical procedures will be verified and will be followed up for 6 months. The cost of which treatment for each participant will be assessed according to the use of health services and calculated by the price list of the Brazil’s Unified Health System and according to the physiotherapist’s fees established by the Federal Council of Physiotherapy and Occupational Therapy and also by average of three budgets for private treatment. Costs will be computed with the use of sanitary napkins, diapers and liners, medications, exams related to urinary problems, consultation with health professionals (such as nurses, doctors and/or physiotherapists), and other interventions and surgical procedures.

In order to compose the economic evaluation, the expenses related to materials used during physical evaluations and intervention (such as gloves, condoms, lubricants, disposable sheets, pressure gauge, NMES devices and probes, and the physiotherapist assessment price) will be computed. In addition, to compose the health costs of tertiary care, information related to hospitalization history, surgery history, average hospitalization time, and absenteeism for health reasons will be verified. To convert the procedures into current currency, the values informed by the Brazil’s Unified Health System price tables and/or based on the market average price will be used. Monetary data will be made in the national currency (real) and converted into international currency with an updated conversion rate.

To compose the indirect costs, the participants will be asked about the days of absence from work (paid or unpaid), which will be computed by means of specific price weights for the female gender and transportation to get to the place where the treatment will be carried out. In addition, the distance between the participants home to the location where the treatment will be applied will be computed. Therefore, the price of the means of transport for those using public transport or weighting of the price of the fuel of private transport will be assessed.

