**Fig. 1 Fig1:**
[figure not shown]
Flowchart of randomized clinical trial. IG1, intervention group 1; IG2, intervention group 2; PFM, pelvic floor muscles; PFMT, pelvic floor muscle training; NMES, neuromuscular electrical stimulation

Two physiotherapists specialist in Women's Health will carry out, guide, and apply the interventions. They will not be involved in the participants’ randomizations, evaluations, or reevaluations. The flowchart is presented in Fig. 1, and the schedule of registrations, interventions, and evaluations are presented in Fig. 2.

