### Minimizing missing data

To avoid and minimize missing data, all participants will receive reminders with the date and time for each session. Physiotherapists responsible for the interventions will also make calls to reinforce the scheduling of sessions. Regarding the evaluations and reevaluations, the blind assessor will contact the participant by telephone, at the end of the 10 treatment sessions, in order to define the best time and date for the reevaluation to be carried out.

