At the interview and physical assessment, the subjective interview record will be applied, which generates qualitative variables that will be presented as frequencies and percentages and quantitative variables that will be presented as minimum value, maximum value, mean, median, and standard deviation. One researcher will perform the vaginal palpation and the manometry assessment, as well as applied SF6-D, KHQ, King´s Health Questionnaire for Scoring Algorithm, health cost analysis form, and 24 h-voiding diary, which will result in quantitative scales that will be presented as minimum value, maximum value, mean, median, and standard deviation.At the end of treatment sessions, vaginal palpation and manometry will be repeated, as well as SF6-D, KHQ, King’s Health Questionnaire for Scoring Algorithm, health cost analysis form, and the 24 h-voiding diary, which will result in quantitative scales that will be presented as minimum value, maximum value, mean, median, and standard deviation.At the 1st to the 6th month of follow-up, the health cost analysis form will be applied, and at the 3rd and 6th month of follow-up, the SF6-D, KHQ, King´s Health Questionnaire for Scoring Algorithm, and health cost analysis form will be completed, which will result in quantitative scales that will be presented as minimum value, maximum value, mean, median, and standard deviation.At the end of the treatment, the ANOVA for repeated measurements will be applied to verify the effects of the three groups and the two stages (pre-treatment and re-assessment after finished the intervention protocol) and the interactions between them according the results related to the vaginal palpation, manometry, SF6-D, KHQ, King´s Health Questionnaire for Scoring Algorithm, health cost analysis form, and 24 h-voiding diary, if the residues present normality. If the residues do not present normality, a non-parametric test will be applied.At the end of the follow-up, the repeated measures ANOVA will be applied to verify the effects of the three groups and the eight stages (pre-treatment, re-assessment after finished the intervention protocol and 1, 2, 3, 4, 5, and 6 months of the follow-up) and the interactions between them considering the SF6-D, KHQ, King’s Health Questionnaire for Scoring Algorithm, health cost analysis form, and 24 h-VD, if the residues present normality. If the residues do not present normality, a non-parametric test will be applied.The cost-utility assessment will be performed by the quality-adjusted life years (QALY), which combines the length and quality of life into a single index number between 0 and 1, where 0 corresponds to a health state judged to be equivalent to death and 1 corresponds to optimal health [35, 36]. To conduct the statistical analysis, the mean between-group cost differences will be corrected for their baseline, and the total costs will be divided by the costs differences for incremental analysis of cost-effectiveness and cost-utility ratios. Subsequently, a deterministic cost-utility value and a probabilistic one will be determined by applying a bootstrapping technique of 5000 interactions and the bias-corrected, in order to compare health costs between groups. The results will be presented with the confidence interval of 95% (95% CI). The likelihood of the cost-effective intervention will be estimated by the cost-effectiveness acceptability curves to compared values other than willingness to pay [37]. The Kaplan-Meier method and the Log-Rank between-group comparison test will be applied in order to assess the sensitivity of the uncertainty of each parameter by assessing the changes in the results in the range of parameter values [38].

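### The article contradicts itself on whether a treating physiotherapist takes part in allocation, and the assessor's cost-data duties put the promised assessor blinding at risk

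*Protocol article*

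**What the plan says.** **Allocation.** The Randomization and allocation section names a researcher "who will not be involved into the participants’ recruitment or treatment, will perform the randomization by the electronic system" and who keeps the sequence in opaque envelopes. It also states that "the initial assessments will be carried out before the participants are randomized (1:1:1) into three groups". Once eligibility is settled, "one physiotherapist responsible for the application of the interventions will open one sealed opaque envelope" and books the start of treatment. The paragraph after Fig. 1, about the two physiotherapists who deliver the interventions, says: "They will not be involved in the participants’ randomizations, evaluations, or reevaluations".

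**Blinding.** The Blinding section says that participants cannot be blinded, but that the evaluating physiotherapist will not know the allocation.

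**Who handles cost data.** In the first detailed item of the Statistical analysis plan, "One researcher will perform the vaginal palpation and the manometry assessment, as well as applied SF6-D, KHQ", and the sentence goes on to include the health cost form. The next items repeat this set after treatment, and apply the cost form every month from month 1 to month 6, with KHQ and SF-6D at months 3 and 6. Data management gives data entry to the physiotherapist in charge of evaluations, repeat evaluations and follow-up.

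**What the cost data contain.** Evaluation tools lists consultations with health professionals, physiotherapists among them, and asks participants about "transportation to get to the place where the treatment will be carried out". Under Interventions the control group receives a booklet, while IG1 and IG2 have weekly supervised sessions.

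**Timing of reassessment.** Under Minimizing missing data, "the blind assessor will contact the participant by telephone, at the end of the 10 treatment sessions" to arrange it.

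**The concern.** The first matter is a contradiction about roles. Opening the envelope that reveals the arm is a step in allocation. One sentence gives that step to a person whom another sentence keeps out of randomisation. A site could follow either sentence and still believe that it was following the protocol.

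The second matter is a conflict between a promise and a list of tasks. The Trial design section presents the study as having a blind assessor. If that assessor hears, or types in, how often a woman travelled for treatment and whether she saw a physiotherapist, the assessor can probably tell a booklet-only woman from a supervised one. This is the contrast in the stated alternative hypothesis, that IG1 and IG2 each differ from the control group.

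The measures most open to influence are palpation, which the examiner grades, and manometry. In both, the assessor gives verbal instruction, and during palpation also encouragement. The KHQ and SF-6D at months 3 and 6 are exposed too, because follow-up outcomes are taken by telephone.

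**Working it through.** The point depends on no sample size, power or event figure, so no formula applies. The check sets the relevant statements side by side.

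**1. Role in allocation**

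| Statement | Place |
|---|---|
| A physiotherapist who applies the interventions opens the envelope and schedules the woman | Randomization and allocation |
| The two treating physiotherapists have no part in randomisation | Same section, after Fig. 1 |

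These agree only if randomisation in the second statement means generating the sequence and nothing more. The text does not say so.

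**2. Does concealment fail?** Four features bear on this:

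- The sequence is generated and held by a researcher outside recruitment and treatment.
- The envelopes are sealed and opaque.
- Allocation is made "by a simple randomization using an electronic system", so past allocations do not predict the next one.
- The envelope is opened after eligibility and baseline assessment.

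The treating therapist therefore learns the arm only after the woman is enrolled. Failure of concealment is not shown.

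**3. Who sees the cost answers after randomisation?** The sentence that names one researcher describes the first visit, when no arm exists yet. The later items name nobody, but they repeat the same set and introduce no one new. Data management then makes the evaluating physiotherapist responsible for repeat evaluations, follow-up and data entry, with no exception for cost data. So even if someone else took the form, the assessor is the person named to enter it. That the assessor takes the form is a strong inference; that the assessor enters the data is stated.

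**4. What the answers reveal.** IG1 and IG2 both attend weekly for 10 weeks, and no supervised sessions are described for the control group. Travel and physiotherapist visits during that period would tend to separate control from the other two arms. They would not separate IG1 from IG2. NMES devices and probes are costed, but are not said to be asked of the participant.

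**5. When**

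| Time | Cost form | Palpation, manometry | KHQ, SF-6D |
|---|---|---|---|
| Before treatment (before allocation) | yes | yes | yes |
| End of treatment | yes | yes | yes |
| Months 1, 2, 4, 5 | yes | no | no |
| Months 3, 6 | yes | no | yes |

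At the end-of-treatment visit the order of procedures is not given. If the outcomes come first, that visit can still be blind. At months 3 and 6 the order within the visit does not help, because the end-of-treatment cost form has already been taken. Counting forms after randomisation, 1 + 2 = 3 come before the month 3 questionnaires (end of treatment, months 1 and 2), and 1 + 5 = 6 come before those at month 6 (end of treatment, months 1 to 5). The end-of-treatment form matters most if, as assumed here, it covers the treatment weeks.

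**6. Anchor of the reassessment call.** The call is tied to the end of the sessions. For the control group, with none described, that date is not defined by attendance.

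**The case against.** Several objections are sound and limit the point.

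- **Concealment.** A reader might infer that a treating therapist who handles envelopes can steer women to arms. The article does not support this, for the reasons in step 2 of the working. It does not state that the envelopes are numbered, but an article may leave that to the full protocol.
- **The contradiction may be one of wording.** The section uses the word for the independent researcher's task, and the later sentence could mean the same. That stands as a possible reading, and one clarifying sentence would settle it.
- **The cost-form route is partly inference.** The items of the form are not shown, and a form filled in after treatment may have no trial travel left to report. A reader might infer that the arm is nearly certain to be revealed at every monthly call. Supervised sessions have ended by then, so the text does not support that.
- **Other blinding exists.** A reader might take assessor blinding to be the only blinding claimed. It is not. The treating physiotherapists do not see evaluations, the principal investigator receives data without group labels, and the analyst is outside evaluation and treatment.
- **Palpation reliability.** Table 2 gives kappa 0.60 between raters and 0.75 within rater. One researcher does the palpation, and neither figure measures bias from unblinding, so neither is used as an argument here.
- **The primary outcomes are reported by unblinded participants.** An unblinded assessor adds less bias there. This is correct.
- **The telephone call.** A scheduling call does not by itself disclose the arm. This too is correct; the weakness is only an anchor that is unclear for one arm.

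What remains is the unresolved statement on allocation, and a blind assessor who is assigned data likely to identify the control arm.

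**Conclusion.** The point holds in two limited parts.

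First, two statements in the same section disagree on whether a treating physiotherapist takes part in allocation, and they must be reconciled. This is a fault in the text, not evidence that concealment fails.

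Second, the promise of a blind assessor conflicts with that person's responsibility for repeat evaluations, follow-up and data entry, once the content of the cost data is considered. Unblinding is likely for control against the supervised arms, and is not shown for IG1 against IG2.

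The bias cannot be quantified from the article. It would fall mainly on palpation and manometry, which are secondary and, after baseline, measured only at the end of treatment. It would fall less on KHQ and SF-6D.

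The second part rests on three assumptions: that the assessor takes the cost form or enters it before the later outcomes are obtained; that the form asks about travel and physiotherapist visits as Evaluation tools describes; and that the end-of-treatment form covers the treatment weeks. If the full protocol gives cost data to other staff, the second part is answered.

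**What to change.** 1. Reconcile the two statements on allocation. One way is to have the independent researcher who holds the envelopes release each allocation once the baseline assessment is recorded, and to tell the treating physiotherapist the result.
2. After randomisation, have the cost form completed by the participant herself, or collected by existing staff other than the assessor. In either case it should be entered by someone other than the assessor. This step protects months 3 and 6, which ordering alone cannot do.
3. At every visit or call, complete whichever of palpation, manometry, KHQ and SF-6D are due before any cost question.
4. Time the reassessment by weeks since randomisation in all three arms, so that the date does not depend on sessions that the control group does not have.

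The cost is a small reassignment of tasks among existing staff and a few sentences of protocol text. Sample size, outcomes and analysis do not change.
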